**Fig. 2 Fig2:**
[figure not shown]
Study flow diagram

### Intervention methods

#### ACT intervention

ACT will incorporate the following elements [15]:

i.Assertive engagement: assertively establishing contact and seeing patients in their homes and/or community settings.ii.Holistic care: addressing physical/mental health and social care needs in a patient-led manner.iii.Building relationships: establishing and maintaining contact, building rapport, working with, and supporting family members.iv.Flexibility: working flexibly with patients’ goals even when their problems seem to be peripheral to addition.v.Openness: being explicit about goals in care planning.vi.Going out of your way: following an ethos of stepping outside of professional roles and going the extra mile for patients.vii.Close follow-up: low staff-to-patient ratio to allow for effective case management and short intervals between reviews.viii.Extended care: intensive case management for 6 months, establishing links with community services and resources, to facilitate long term support.

ACT will be used to proactively engage with ARFA patients, to assess their physical and mental health and wider social needs, then to develop shared treatment goals, and to facilitate and coordinate engagement with the relevant care and support to address their multiple presenting needs. The ACT will mainly take place either in the patient’s home or local community settings.

#### The multidisciplinary team-based ACT intervention

Historical patient data are collected from the electronic health record system. We implement a multidisciplinary, team-based ACT intervention, targeting medical, psychiatric/psychological, social and substance (MPSS) domains. The ACT teams follow a predefined schedule, with each engagement spanning approximately 60 min. Interactions include CM and collaboration with a social service agency (SSA). Patients who opt out of the intervention will still be considered in the analysis.

The ACT team will maintain active engagement with ARFAs on a schedule detailed (see S Table 1), with a typical interaction lasting 60 min.

Each visit is not rescheduled in the event of a patient’s absence; instead, the team will re-engage the patient via phone to plan for the succeeding visit as per schedule. Consistent with the core principles of ACT, ARFAs are assertively engaged in the community, receiving intensive, comprehensive, and supportive care with a harm reduction approach. This also incorporates CM and collaboration with a SSA.

A typical ACT visit is as outlined in Fig. 3. “Assertive” in ACT means ACT workers lean forward in terms of patient recruitment and retention. This involves visiting patients in various non-traditional settings including but not limited to hospital admissions, nursing homes and incarceration. If the patient is uncontactable for individual visits, the research worker will go around the vicinity to look for the patient. In the event that a patient falls out with the research worker, an option to switch the research worker is available, as it is a counselling-based intervention.

**Fig. 3 Fig3:**
[figure not shown]
Example of a typical ACT visit

Each ACT intervention interaction encompasses various facets of physical health, mental health, and addiction. The ACT team will address problems across the four life domain categories of MPSS. Weekly multi-disciplinary team (MDT) meetings will be held for problem discussions following the MPSS format.

Given the community-based nature of ACT, ARFAs may be encountered at various locations beyond their residences. Privacy is prioritized during all interactions. ARFAs are briefed about the limitations of confidentiality, and consent is obtained prior to each session. CM elements, including phone call reminders for medical appointments, psychoeducation, and medication assistance, will be provided.

#### Teamwork, training, and continuing education

The core ACT team, consisting of physicians, nurses, and allied health practitioners, receive training and support from national addictions management service.

The team members undergo intensive training in motivational interviewing and cross-cultural competencies, along with specific courses on adequate social assistance referral. Formal training sessions are conducted prior to the launch of ACT services at each participating hospital, with a stipulated data collection schedule attached in Additional file 2 (see Additional file 2).

#### Data monitoring

Our study is overseen by ARFA steering committee consisting of PIs and Co-PIs of this study. The committee ensures the safety and efficacy of data collection and the ethical conduct of the trial. No members of the committee have competing interests in the trial’s outcomes. Interim analyses are conducted during ARFA’s follow-up. The primary purpose of these analyses is to assess safety parameters and to check for any unforeseen risks. An independent audit will be conducted yearly by the hospitals to ensure the trial’s conduct aligns with the approved protocol and good clinical practice guidelines.

#### Primary outcome: number of ED visits

The primary outcome is the number of ED visits by ARFAs, sourced primarily from the electronic records system of the participating hospitals. A comparative analysis will be conducted between the rates of ED visits pre-intervention (12 months) and post-intervention (12 months).

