**Methods:**

Employing a prospective before-and-after cohort design, this investigation targeted ARFAs aged 21 years and above, fluent in English or Mandarin. Eligibility was determined by a history of at least five ED visits in the preceding year, with no fewer than two due to alcohol-related issues. The study contrasted health outcomes of patients integrated into the ACT care model versus their experiences under the exclusive provision of standard emergency care across Hospitals A, B, C and D. Following participants for half a year post-initial assessment, the evaluation metrics encompassed socio-demographic factors, ED, and EMS engagement frequencies, along with validated health assessment tools, namely Christo Inventory for Substance-misuse Services (CISS) scores, University of California, Los Angeles (UCLA) Loneliness scores, and Centre for Epidemiologic Studies Depression Scale Revised (CESD-R-10) scores.

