### Primary hypothesis

ACT is expected to be more effective than standard care in reducing the annual number of ED visits by ARFAs, as measured at a 12-month follow-up.

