### Secondary hypotheses

ACT is expected to improve health outcomes compared with standard care at a 12-month follow-up.ACT is expected to be more cost-effective compared with standard care at a 12-month follow-up.

The study protocol comprises a total of 17 visits, including a follow-up at six months post-final assessment. The intervention manual and comprehensive study protocol is adhered to the Standard Protocol Items: Recommendations for Interventional Trials (SPIRIT) attached in Additional file 1 (see Additional file 1) and can be made available upon request from the authors.

Employing a before-and-after study design will facilitate measurements of ACT outcomes in ARFAs before and after its formal implementation in EDs. Changes in ARFAs’ outcomes will thereby be attributed to the ACT intervention. Previous ARFAs ED usage data serves as a control group for comparative analysis. While this design does not negate the need for randomization, it offers a more pragmatic approach that can be less resource-demanding than a randomized-controlled trial (RCT). Importantly, the study can be executed concurrently with standard ED operations.

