#### Screening and recruitment

Patients who meet the inclusion criteria are identified through clinical referrals within each participating hospital using alcoholism codes ICD-10-AM, SNOMED and ICD-9-CM codes. Each hospital’s ACT teams prioritize recruitment for those who have most frequently used ED services, with the aim to recruit up to 17 patients over six months (equating to 34 patients per year).

Four hospitals participate in the study over a four-year period (see Table 1). Recruitment of participants for each site is done yearly and staggered. Considering Singapore’s limited resources, and the existence of only one tertiary addiction centre, the study initiation dates are strategically staggered to ensure sufficient supervisory support.

**Table 1 Tab1:** Details of recruitment

Intervention Site	Date of Initiation	Date of completion	Maximum Subjects
Hospital A	August 2020	February 2024	136
Hospital B	August 2021	February 2024	102
Hospital C	August 2022	February 2024	68
Hospital D	August 2023	February 2024	34

Invitations to partake in the study are extended via phone calls, offering potential subjects a week for consideration. However, pilot data suggest a significant proportion of ARFAs are homeless and lack phone access. As such, an opportunistic recruitment approach is primarily adopted, enabling engagement with eligible patients during their hospital visits. Members of the study team approach eligible patients, extending an invitation to participate and providing necessary information, including the need for retrospective data sharing consent. The consent is obtained by either Site-Principal Investigators (PIs) or Co-Investigators (Co-Is).

To optimize participant retention and ensure complete follow-up, we have implemented strategies that emphasize flexibility and participant engagement. Regular check-ins, either by phone or text, will maintain consistent communication, while appointment schedules are tailored to participants’ availabilities. If participants discontinue or deviate from the intervention protocol, we will attempt an exit interview to gather insights and continue collecting relevant outcome data, ensuring that their contribution remains valuable and meaningful to the study.

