#### Secondary outcomes: cost analysis & health outcomes

*Cost Analysis*: The secondary outcome will first focus on the cost implications of healthcare resource consumption by ARFAs. We will analyse the costs generated at participating hospitals but cannot incorporate costs incurred at non-participating community institutions. We will calculate the net cost savings by comparing the cost of ACT during the intervention period against the cost savings from decreased ED encounters in the 12 months post-intervention.*Health Outcomes*: We will measure ARFA outcomes using the Christo Inventory of Substance-misuse Services (CISS) score, a validated marker of alcohol dependence severity, and the UCLA 3-point Loneliness Scale, a quick method for assessing social isolation. Furthermore, we will use the Center for Epidemiologic Studies Depression Scale Revised (CESD-R-10) to measure depression. Comparisons will be drawn between pre-ACT and post-ACT scores after six months of treatment.

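### The follow-up window for the primary outcome is stated inconsistently, and Table 1 does not say whether its February 2024 date ends recruitment or data collection

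*Protocol article*

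**What the plan says.** The protocol article describes the follow-up for ED visits in several places.

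- Abstract, Methods: "Following participants for half a year post-initial assessment", with ED and EMS frequencies listed among the metrics.
- Primary hypothesis: "reducing the annual number of ED visits by ARFAs, as measured at a 12-month follow-up". No start point is given.
- Secondary hypotheses: the 17 visits include "a follow-up at six months post-final assessment".
- Primary outcome: "A comparative analysis will be conducted between the rates of ED visits pre-intervention (12 months) and post-intervention (12 months".
- Cost analysis: the cost of ACT during the intervention period is set against "the cost savings from decreased ED encounters in the 12 months post-intervention". The intervention period and the 12 months are thus separate.
- ACT intervention: intensive case management lasts 6 months.

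On the calendar, Screening and recruitment says "Four hospitals participate in the study over a four-year period". Table 1 then gives initiation dates of August 2020, 2021, 2022 and 2023 for Hospitals A to D and one completion date, February 2024, for all four. The table's caption refers to recruitment, while the sentence introducing it refers to participation in the study. Statistical methods plans a paired t-test or Wilcoxon signed rank test on ED utilization before and after.

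**The concern.** In a before-and-after study with no concurrent control, the two windows define the effect being estimated. Months 1–12 from enrolment and months 7–18 answer different questions. The first includes ED visits while ACT is being delivered; under the second, those visits fall in neither the before nor the after period. A half-year window cannot yield an annual after-count at all. If the choice stays open, it could be made after the results are seen.

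The calendar adds a second problem. If data collection stops in February 2024, late enrolees cannot complete a 12-month window. The paired tests named in Statistical methods carry no term for observed time, so incomplete windows entered as raw counts would look like fewer visits even if ACT did nothing.

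**Working it through.** **The plan's own figure.** The sample size is built on annual visits: mean 30.15, expected decrease 40%, SD 23, 80% power, alpha 0.05 (taken as two-sided).

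- Difference = 0.40 × 30.15 = 12.06 visits.
- n = ((1.960 + 0.842) × 23 / 12.06)² = 28.55, so 29.

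The stated 29 reproduces. The point does not rest on the sample size, but it shows that the planning unit is a full year of visits.

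**The windows side by side**, counted from enrolment with 6 months of ACT:

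| Source | After-window | Ends at month |
|---|---|---|
| Abstract | half a year from initial assessment | 6 |
| Primary hypothesis | 12-month follow-up, origin not given | 12 if from enrolment, 18 if from end of ACT |
| Primary outcome and cost analysis | 12 months post-intervention | 18 on the natural reading |

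The first row cannot be matched to the others. The second and third agree only if the hypothesis's clock starts when ACT ends.

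**Reading 1: February 2024 is the end of data collection.** Months of entry that leave a full window = months from opening to February 2024, minus 12 (from enrolment) or 18 (12 months after ACT), not below zero.

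| Hospital | Months open | Full 12 months from enrolment | Full 12 months after ACT |
|---|---|---|---|
| A | 42 | 30 | 24 |
| B | 30 | 18 | 12 |
| C | 18 | 6 | 0 |
| D | 6 | 0 | 0 |
| Total | 96 | 54 (56%) | 36 (38%) |

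At the stated ceiling of 17 patients per six months, this is 54/6 × 17 = 153 or 36/6 × 17 = 102 of 96/6 × 17 = 272 patients.

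**Reading 2: February 2024 is the end of recruitment.** The last enrolee's window ends in February 2025 (12 months) or August 2025 (18 months). Four years from August 2020 end in August 2024. The stated accrual also falls short of the stated maxima:

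- A: 42/6 × 17 = 119, against 136
- B: 30/6 × 17 = 85, against 102
- C: 18/6 × 17 = 51, against 68
- D: 6/6 × 17 = 17, against 34

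So neither reading fits everything the article states.

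**Size of the risk if raw counts were compared.** Assume uniform entry, a February 2024 cut, a constant visit rate and no effect. A hospital open S ≥ 12 months contributes (S − 12) × 12 + 72 units of entry-month × observed month; one open S < 12 contributes S²/2.

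- From enrolment: 432 + 288 + 144 + 18 = 882. Mean window 882/96 = 9.19 months; apparent fall 1 − 9.19/12 = 23%.
- From end of ACT, S reduced by 6: 360 + 216 + 72 + 0 = 648. Patients with any post-ACT time entered over 36 + 24 + 12 = 72 site-months. Mean window 648/72 = 9.0 months; apparent fall 1 − 9.0/12 = 25%.
- A raw 6-month count, as in the abstract: 30.15/2 = 15.08 visits, an apparent fall of 50%. The planned 40% effect leaves 18.09 visits.

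**The case against.** There is a good deal to say on the other side.

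- A reader might infer three mutually incompatible windows. That goes too far. The hypothesis gives no origin, so it and the primary outcome can be the same window. The visit at six months after the final assessment belongs to the contact schedule, whereas ED counts come from electronic records. Only the half-year version conflicts on every reading.
- A reader might also infer that the plan sets a full before-year against a shortened after-period. No section says so. The Primary outcome section gives 12 months on each side and speaks of rates. Statistical methods mentions complete-set analysis and imputation, and further handling may sit in an analysis plan not shown.
- The Table 1 shortfall is conditional. The caption points to recruitment, and records can be extracted after hospital participation ends. Fig. 1 (the inclusion and follow-up timetable) and Additional file 2 (the data collection schedule) are not shown and may settle it.
- The accrual of 17 per six months is a ceiling. It implies about (31 + 19 + 7) × 17/6 = 162 patients at Hospitals A to C by March 2023; Preliminary results reports 93. The 56% and 38% therefore describe the calendar, not the actual cohort. Even 102 complete windows exceed the 29 patients required.

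Most of this stands, and it limits the point. It does not remove the conflict between the abstract and the body, the missing origin, or the undefined completion date. These are conflicting or unclear statements of the primary endpoint, not detail left out for brevity. Having enough complete windows for power does not settle which window is primary.

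**Conclusion.** The point holds as an inconsistency in the primary-outcome window, together with a calendar that may not supply that window. The inconsistency needs no assumption. The 56% and 38% require February 2024 to be the end of data collection and entry spread evenly over the months each site is open. The 23–25% falls further require that incomplete windows be compared as raw counts; the 50% figure applies only to a raw 6-month count set against a full year. Using rates, as the Primary outcome section suggests, would remove this bias if the visit rate is steady, but the paired tests on utilization are not tied to rates. Truncation bias is therefore a risk the plan leaves open, not something it prescribes.

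A reader might also arrive at a 44% fall for the post-ACT window (1 − 6.75/12, with 6.75 = 648/96) and note that it exceeds the planned 40%. That figure scores patients with no post-ACT time as having zero visits. They have no after-value and cannot enter a paired test; without them the figure is 25%.

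**What to change.** 1. State one primary window and its origin, either enrolment or the end of ACT. The choice is the sponsor's. Use it in the abstract, both hypothesis sections, the primary outcome and the cost analysis. Report the other window as secondary, so that ED visits during ACT are also shown.
2. Label the February 2024 date in Table 1 as end of recruitment or end of follow-up, and reconcile it with the four-year period and the site maxima.
3. Set the electronic-record extraction date so that the last enrolee at every hospital has the full window.
4. Where a window is still incomplete, analyse the visit rate with log observed time as offset, keeping the within-patient pairing, and do not compare raw counts. The offset assumes a roughly steady rate over the window, so it supplements step 3 and does not replace it.

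The cost is wording and a later record extraction, with no added patient visits. The downside is a later read-out for the late-opening hospitals.

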#### Secondary outcomes: cost analysis & health outcomes

*Cost Analysis*: The secondary outcome will first focus on the cost implications of healthcare resource consumption by ARFAs. We will analyse the costs generated at participating hospitals but cannot incorporate costs incurred at non-participating community institutions. We will calculate the net cost savings by comparing the cost of ACT during the intervention period against the cost savings from decreased ED encounters in the 12 months post-intervention.*Health Outcomes*: We will measure ARFA outcomes using the Christo Inventory of Substance-misuse Services (CISS) score, a validated marker of alcohol dependence severity, and the UCLA 3-point Loneliness Scale, a quick method for assessing social isolation. Furthermore, we will use the Center for Epidemiologic Studies Depression Scale Revised (CESD-R-10) to measure depression. Comparisons will be drawn between pre-ACT and post-ACT scores after six months of treatment.

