### Objectives

To conduct a before-and-after trial of ARFAs in four public hospitals under three healthcare clusters in Singapore.To evaluate the effectiveness and cost-effectiveness of ACT intervention for ARFAs as compared to standard care in the emergency departments.To describe the patient characteristics, ED care characteristics and health outcomes of ARFAs.

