### Statistical methods

Continuous variables will be reported as mean and standard deviation using Student’s t-test. Categorical variables will be reported as frequency count and percentage using Chi-square test/Fisher’s exact test. Univariate analysis will be done to select variables for an adjusted multivariable analysis. Statistical significance will be set at P < 0.05 criteria. We will adopt imputation to address missing data.

Using complete set data analysis, cases undergoing ACT will be compared their own historical outcomes as controls. ED utilizations will be compared using the paired sample t-test or Wilcoxon Signed Rank test, the post-intervention utilization of ARFAs undergoing ACT will be compared to the pre-intervention utilization.

To adjust for potential confounders, multivariable regression analysis will be undertaken. Interactions will be tested for variables that are clinically relevant and are statistically significant. Model adequacy will be assessed through coefficients of determination (R2) and by plotting error terms against predicted values. Presence of multicollinearity will be evaluated by variance inflation factor (VIF). Should complete set analysis show efficacy, we will proceed to analyze the data using an intention-to-treat analysis.

The incremental costs of delivering the intervention will be estimated and compared to any observed cost savings from reduce usage of ED services and other health services. All analyses will be performed using R 4.2.0 (www.r-project.org) and STATA version 17.0 (StataCorp. 2017. Stata Statistical Software: Release 17.0. College Station, TX: StataCorp LLC) software.

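### The two cost sections of the protocol article define different savings, neither says that increased use of other services is charged, and both give a net cost offset rather than the promised cost-effectiveness

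*Protocol article*

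**What the plan says.** The Protocol article speaks to cost in four places.

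- **Objectives:** "To evaluate the effectiveness and cost-effectiveness of ACT intervention for ARFAs as compared to standard care in the emergency departments".
- **Secondary hypotheses:** "ACT is expected to be more cost-effective compared with standard care at a 12-month follow-up".
- **Secondary outcomes (cost analysis):** "We will analyse the costs generated at participating hospitals", with the stated limit that the authors "cannot incorporate costs incurred at non-participating community institutions". Net saving is then obtained by "comparing the cost of ACT during the intervention period against the cost savings from decreased ED encounters in the 12 months post-intervention".
- **Statistical methods:** the incremental cost of delivering ACT is compared with "any observed cost savings from reduce usage of ED services and other health services". No time window is given.

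Two other parts bear on this. The ACT intervention section describes "intensive case management for 6 months, establishing links with community services and resources, to facilitate long term support". The Discussion accepts that ACT may lead to a patient being institutionalised, and it expects the findings to inform on cost-effectiveness and on savings for the national health system.

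**The concern.** A reader who follows the secondary-outcomes section computes one net saving; a reader who follows Statistical methods computes another. The first credits ED encounters only, the second ED and other services. Both speak of savings from lower use, and neither says what happens if inpatient or outpatient use at the same hospitals rises. ACT coordinates care across medical, psychiatric and social needs, so such a rise is plausible.

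The period is also unclear. ACT is charged during the intervention, savings are counted over 12 months post-intervention, and the hypothesis is set at 12-month follow-up. Whether these describe the same 12 months depends on when post-intervention begins.

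Finally, neither section ties a cost to a unit of effect. ACT could be cost-effective without saving money, or save money without improving health. A net saving reported under a cost-effectiveness heading would be read as answering a question that it does not address.

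**Working it through.** **Inputs.** Baseline ED use of 30.15 visits per year, a 40% expected decrease and SD 23 (Trial flow and sample size). ACT lasts 6 months (ACT intervention). Baseline and after windows are 12 months each (Primary outcome). The article gives no ACT cost, no ED unit cost and no net-saving figure, so the check counts ED visits.

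**The plan's own figure.** Planned effect: 0.40 × 30.15 = 12.06 visits per patient-year. With two-sided alpha 0.05 and 80% power, the paired normal approximation gives n = (23 × (1.960 + 0.842) / 12.06)² = 28.55, so 29. This matches the stated 29 and confirms 12.06 as the planning effect.

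**1. Two definitions.** Let C be the ACT cost, E the ED saving and H the net saving in other services (negative if their use rises).

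- Secondary outcomes: net saving = E − C.
- Statistical methods: net saving = E − C plus any saving in other services.
- Full ledger: net saving = E + H − C.

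If E < C < E + H, the first two have opposite signs for the same patients. If H is negative, E − C overstates the hospital saving by |H|, and Statistical methods does not say that |H| is deducted. Whether either case occurs cannot be shown without unit costs.

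**2. The window.** Six months of baseline use is 30.15 / 2 = 15.075 visits. The article does not say what happens to ED use during ACT. I assume a range from a 20% rise to a 40% fall: −0.20 × 15.075 = −3.02 to 0.40 × 15.075 = +6.03 visits avoided. After ACT I take the planned 40% fall throughout.

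| Window | Visits avoided per patient |
|---|---|
| 12 months after ACT ends | 12.06, whatever happens during ACT |
| 12 months from ACT start (6 ACT + 6 after) | 6.03 + (−3.02 to 6.03) = about 3.02 to 12.06 |
| 18 months from ACT start | 12.06 + (−3.02 to 6.03) = about 9.04 to 18.09 |

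If post-intervention starts when ACT ends, service use in 6 of the 18 months after ACT start (6/18 = 33%) enters neither side. The omission ranges from −3.02 to +6.03 visits, so it can flatter or penalise ACT. If the period starts with ACT, the omitted share is 0%.

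**3. Costs moved outside the hospitals.** Suppose care at non-participating institutions costs the equivalent of 1, 3, 6 or 12 ED visits per patient (assumed). As a share of the 12.06 credited visits this is 1/12.06 = 8%, 3/12.06 = 25%, 6/12.06 = 50% or 12/12.06 = 100%.

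**4. Cost against effect.** Set side by side, the Objectives and Secondary hypotheses name cost-effectiveness. Secondary outcomes and Statistical methods name cost minus saving. Neither of these last two links a cost to an effect.

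**The case against.** The strongest reply is that this is a condensed article about a secondary outcome, and that effect measure, perspective and ratio may stand in a full protocol that is not shown. That is fair for missing detail. It does not cover a net-saving rule that the article does state, that its own Statistical methods section contradicts, and that answers a narrower question than the hypothesis.

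Three stronger readings are tempting, and the documents do not support them.

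- **That a third of the period is certainly uncosted.** The follow-up described under Secondary hypotheses falls six months after the final assessment. With six months of ACT, this also allows 12 months from ACT start, and then nothing is left out. Charging a cost first and counting benefit later is not an error in itself.
- **That the formula is tilted towards saving by construction.** The ACT months can bias either way, and at the planned effect leaving them out understates the saving by 6.03 visits. Only unrecorded increases in other services and shifted community costs would favour ACT.
- **That all non-ED care is costed at zero, or that the trial can support no cost statement.** The article says that costs at participating hospitals will be analysed. Only the net-saving sentence is confined to ED encounters. The community exclusion is openly disclosed as a data limit, and how often patients are institutionalised is not stated.

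**Conclusion.** The point holds as a conflict between two stated definitions and as a mismatch between calculation and hypothesis. As written, the secondary-outcomes rule leaves any rise in inpatient or outpatient use at the same hospitals out of the net figure, and Statistical methods does not clearly bring it in. What results is a net cost offset to participating hospitals.

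The window matters, but conditionally. The ED visits credited are 12.06 per patient on one reading and 3.02 to 12.06 on the other, given the planned 40% fall and my assumed range during ACT. The community exclusion is a declared limit. It still matters because ACT works by "establishing links with community services and resources, to facilitate long term support", so a cost moved out of the hospitals can appear as a saving. The visit-equivalents above show how large that would have to be; they do not estimate it. This should be put right before the cost results are analysed, and it does not affect the primary outcome.

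**What to change.** Reconcile the two sections into one ledger with one window.

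1. Count 12 months from ACT start, which matches the 12-month hypothesis and the 12-month baseline. A longer baseline is then not needed.
2. On the after side include ACT delivery and all ED, inpatient and outpatient costs at participating hospitals, increases as well as decreases. Compare with the same service categories in the 12-month baseline.
3. Report mean net cost per patient with a 95% confidence interval, and incremental cost per ED visit averted, with the visits counted over the same window as the costs.
4. Add a threshold analysis: the unobserved community or institutional cost per patient at which the saving disappears.

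If cost will not be related to effect, restate the objective and hypothesis as net cost to participating hospitals.

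The price is revised wording and extra extraction of inpatient and outpatient costs at hospitals already in the study, with no new patient procedures. The stated saving may turn out smaller.
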